1. OBJECTIVES
   1. Main objective

The main objective of the study is to show improvement in the quality of life among Parkinson’s patients following a therapeutic education program compared with Parkinson’s patients who do not follow such a program.

- 1. Secondary objectives

The secondary objectives of the study are to compare the motor condition, psychological condition, social adjustment and medical costs of two groups of Parkinson’s patients.

- 1. Research hypothesis and results expected

The results expected are an improvement in the quality of life of Parkinson’s patients who follow a therapeutic education program compared with Parkinson’s patients who do not follow such a program.

This improvement in quality of life may be correlated with an improvement in the psychological condition and/or motor condition.

We hypothesize that there will be a cost differential in favor of the Parkinson’s patients who follow a therapeutic education program.

1. METHODOLOGY
   1. Experimental plan

The study is an open, randomized, monocentric, comparative prospective study of 2 groups of Parkinson’s patients (the first following a therapeutic education program, the second not following this program).

The Parkinson’s patients will be randomly assigned to group I (patients following the therapeutic education program) and group II (patients not following the therapeutic education program).

In both groups, patients will undergo a clinical assessment before randomization and after 6 and 12 months of inclusion. This assessment calls for completing a self-assessment questionnaire that aims to assess quality of life, anxiety, depression and social consequences for these patients. Furthermore, at each visit, neurologists specialized in Parkinson’s disease will carry out a clinical examination notably including a motor assessment. Lastly, at each visit, the patients will give hand in a notebook in which they systematically note each medical consultation (specialized or not) and each hospitalization in order to undertake a medico-economic assessment.

Patients in both groups will undergo regular, conventional follow-ups by their referring neurologist.

[figure not shown]

|  | Visit 1: 1st month | Visit 2: 6th month | Visit 3: 12th month |
| --- | --- | --- | --- |
| Informed consent | X |  |  |
| Randomization | X |  |  |
| Self-assessment questionnaires | X | X | X |
| Clinical examination | X | X | X |
| Filling in the notebook | X | X | X |

We have chosen to carry out a pragmatic study in order to respect the patient’s usual living conditions. We are therefore seeking to interfere as little as possible in the usual care outside the TEP visits.

- 1. Therapeutic Education Program (TEP)

This Therapeutic Education Program was developed following the recommendations proposed by France’s Haute Autorité de Santé in its guidebook: *Guide Méthodologique-Structuration d’un programme d’éducation thérapeutique du patient dans le champ des maladies chroniques*, (*Methodological Guide-Structuring of a Patient Therapeutic Education Program in the Field of Chronic Diseases*) Haute Autorité de Santé-INPES, June 2007, and according to the recommendations for caring for Parkinson’s patients in the guidebook *Syndromes Parkinsoniens dégénératifs ou secondaires non réversibles (Degenerative or secondary non-reversible Parkinsonian Syndromes)* published by the Haute Autorité de Santé. On this basis, our team, made up of a registered nurse with training in therapeutic education ([name]) and neurologists specialized in IPD (Drs. [name] and [name]), drew up a therapeutic education program applied to patients suffering from IPD.

This program is carried out in 3 steps, which are:

### Step 1: The Initial Education Consultation

This precedes any educational intervention. Its content will be recorded in the education file and will remain confidential. It lasts 45 minutes, to be adapted depending on the patient’s possibilities. The Initial Consultation is carried out by [name] and comprises two steps:

- Establishing the educational diagnosis;
- Establishing the education contract and the patient’s program.

The **educational diagnosis** is the starting point of the education process; it is the first meeting between the patient and the healthcare professional. It enables the healthcare professional to gather precise information by gaining an understanding of the various dimensions of the patient’s life (family data, socioprofessional data, understanding of the disease, representations and beliefs in terms of healthcare, impressions and acceptance of the disease, the patient’s projects).

With this questioning, the healthcare professional gains a better understanding of patients, their personal and social resources, their reactions in confronting the disease, their motivations and blocks to the educational process. Likewise, it will help them to think about their acts and their perception of the situation by helping them to realize what they know and what they do not know.

For patients, the **educational diagnosis** is the start of the education process. It enables them to talk about themselves, their beliefs and their convictions. Patients can express their needs, their fears and their emotions. Through talking about their lives, they describe their experience with the disease, which enables them to understand what they know, what they do and how they do it, highlighting the merits of their actions. They can express their expectations for support and education.

The next step will be to work together to find ways to improve how they manage the disease, determining the skills they need to acquire or mobilize and the resulting educational goals. These goals will be precise and realistic. Patients have to understand their usefulness in everyday life and the interest they have in applying them. They should not feel that they are too complicated and therefore unachievable. It will be interesting to place priority on educational goals that have an immediate impact on the patient’s everyday life and health. The aim is to provide relief, but also to stimulate the learner’s interest and motivation.

Alongside the educational goals, there are more personal goals dealing with the patient’s specific needs and their project. These are an indispensable source of motivation for patients to comply with the program. Defining all these goals will lead to an individualized, negotiated **education** **contract**. The patient’s agreement will not only cover the goals to be met, but also the choice of the means to be used and the organization of the personalized program (what type of consultations, frequency, appointment dates and times, group days).

For this consultation, our therapeutic education nurse will be assisted by an interview guide to be used for gathering information and as a structured support for dialogue.

EDUCATIONAL DIAGNOSIS INTERVIEW GUIDE

***Assessment of physical, sensory and cognitive skills:***

***Mobility:***

*Pain: Speaking:*

*Swallowing: Vision:*

*Elimination: Hearing:*

***Memory, cognitive disorders****:*

***Other:***

***Biomedical aspects (1), severity of the disease, disability and health problems, what he/she has:***

How long have you had Parkinson’s disease? (disease case history, hospitalizations, pain, miscellaneous disabilities).

How does the disease manifest itself, which symptoms bother you the most?

*Do you have other health problems? If so, what ones?*

***Socioprofessional and family aspects (2), family environment, activities, living conditions, what he/she does:***

*How do you organize your everyday life? What are your days like?*

*Personal health practices, sleep, naps, eating habits, miscellaneous difficulties:*

*Living environment (adjustment to needs):*

*Individual home (floors):*

*Apartment (floors, elevator):*

*Assisted living facility:*

*Retirement home, with medical services/non-medical:*

*Other:*

*Way of life, family environment:*

*Collective: Alone:*

*With family, describe family members:*

*Spouse’s activity:*

*Children or dependents:*

*Have you changed your usual activities? In what way?*

*Everyday habits:*

*Physical activities:*

*Leisure, pastimes, vacation:*

*Travel methods, trips:*

*Associations:*

*Profession: Social status:*

*Working: Medical leave:*

*Adapted workstation: Extended medical leave:*

*Job-seeker: Assistance (MDPH – public assisted living facility):*

*Retired: Long-term disorder:*

*Do you receive specific social assistance? What kind? How do you live with disabilities, preservation or adaptation of professional activities?*

***Socioprofessional and family aspects (2), family environment, activities, living conditions:***

*How do you organize your life during difficult periods?*

*(managing fluctuations in motor conditions in everyday life, preserving autonomy)*

*What have you tried to set up to improve your situation, so that you feel better?*

*(changing one’s living habits, adapting your home, use of technical aids, adjustment strategy)*

*Have you called upon outside help?*

*(decision-making, self-assessment of one’s difficulties, amount of information on the aid available, what aid)*

*Who do you go to for your health problems? When?*

*(decision-making, assessment of one’s difficulties, choice of the practitioner, general practitioner, neurologist, other)*

***Cognitive aspects (3), knowledge, representations and beliefs concerning health and treatment, what he/she knows:***

*Can you tell me what you know about this disease?*

*What do you think your disease is caused by?*

*Do you know other people who have this disease?*

*What effects do the treatments you take have? (description, categories, perception, beliefs)*

*How do you take your treatment? Do you sometimes forget to take it or do you take more? (forgetting, addiction, managing doses, getting out of bed, pill organizer, locus, beliefs)*

*How do you feel about your treatment? (satisfactory, constraint, tolerance, etc.)*

A summary of the educational diagnosis is drawn up and submitted to the education team at the monthly education team meeting.

| **SUMMARY OF THE EDUCATIONAL DIAGNOSIS**  **Date:**  **Last name: First name:**  **Referring physician:** |
| --- |
| Biomedical context, seriousness of the disease, disability and health problems, what he/she has: |
| Socioprofessional context, family environment, activities, living conditions, what he/she does |
| Knowledge, representations and beliefs in the area of health and treatment, what he/she knows: |
| Psychoemotional context, impressions, attitudes, acceptance of the disease, self-esteem and locus, what he/she is: |
| Expectations, patient needs, personal project, what projects do they have: |
| Objectives, skills to be acquired or developed: |
| Difficulties, limiting factors:  Assets, motivation: |

### **Step 2 – The Individual Education Consultation**

Each consultation is organized around an educational goal in direct relation with the skills to be acquired.

Its duration may vary between 30 and 45 minutes. This will depend on the complexity of the goal for the session and the patient’s possibilities, which may fluctuate.

**Conduct of the session**:

- Start: presentation of the goals and the conduct of the session, validation by the patient;
- Take the patient’s motor or thymic condition into account, with his/her ability to concentrate;
- Make use of the participant’s knowledge and experience to give meaning to the learning process;
- Use communication techniques that focus on the person, such as active listening and motivational counselling, to initiate a change in the patient and support his/her motivation;
- Alternate between tools and methods to be chosen in relation to the topic of the session (three at most): posters, folder/picture-word books, videos, CD-ROMs, documentary testimonials, brochures, simulations of gestures and techniques;
- Assessment of the patient’s ability to apply the knowledge acquired in everyday life thanks to simulations based on the analysis of a situation (case studies);
- End-of-session summary with the learner’s participation, this helps the learner to make the content of the session his/her own.

**3- Telephone TEP sessions:**

These can be used during the education program between two individual sessions, but can also be organized upon request from the patient or the nurse during a consultation for a one-off session. It will deal with the implementation of a new skill whose acquisition is felt to be difficult and which requires closer monitoring. It will be used to analyze the situation with the patient, to find solutions to the problems that arise and to boost motivation.

This type of session will give rise to a telephone meeting and will not be at the patient’s expense. It will be followed by an individual consultation, either to reinforce the learning process depending on the level of difficulty encountered, or to pursue the educational coverage. It will be rounded out by a report in the education file.

**4-Group sessions, Theme Days:**

Group sessions will be offered to patients who follow an education program. They will give rise to specific work depending on the theme of the day, which will be selected in relation to the participants’ educational goals.

These sessions will be held approximately every two months, during an outpatient visit, from 9:00 am to 4:30 pm. They will include 6 to 8 patients on average, as well as family members or friends who would like to attend. They are hosted by the registered nurse who accompanies the group for the whole day and a physician from the education team.

They will be structured as follows:

**Presentation session** (duration: 30 min.): Welcome, presentation of the program (duration, subjects, times, breaks, meals, location of the rest rooms) and the coordinators. Introduction round: a quick initial contact between the patients and the coordinators who are present.

**Educational sessions** lasting 40 to 45 min., separated by breaks lasting at least 10 min. to give the patients an opportunity to move around and to take their medications. There will be approximately three breaks during the day.

At the start of the afternoon, a simulation with a concrete case study will be proposed in a **wrap-up and assessment session**. This is an opportunity to take stock of how well the key points covered during the day have been understood and to prepare the transfer of the knowledge acquired into everyday life. A satisfaction questionnaire will be distributed during the last break before the Clarification Workshop session that closes out the day.

**The Clarification Workshop** is an opportunity to express one’s feelings about the day and to ask questions that the participants had not dared to ask earlier.

An individual consultation will be organized approximately once a month after the training to assess the acquisition of the knowledge and skills taught, check that they are applied and, if necessary, review those notions that were not fully understood.

**4-The Individual Assessment Consultation** is designed to highlight and promote the transformations obtained in terms of skills and improvement in quality of life.

It is proposed after 6 months of follow-up and earlier if necessary, whether at the patient’s or healthcare professional’s request. This consultation gives rise to an update of the educational diagnosis, the educational goals and, if necessary, a change in the content of the program proposed at the start of care.

This assessment covers the following elements:

- Formative assessment of the skills acquired, to be maintained, to support and to complete;
- Assessment of quality of life, self-esteem, acceptance of the disease;
- Assessment of the educational diagnosis: did the educational goals meet the patient’s expectations, are they still suited to his/her needs, to the progression of the disease, to changes in treatment, to changes in his/her professional, family or emotional life, to his/her life projects.
- Assessment of patient satisfaction: this is used to gather personal feelings about the educational care received and to make any corrections needed, but also to gather the patient’s point of view on the TEP program and on its relevance, the difficulties encountered, and to assess the organization and conduct of the sessions.

The same kind of assessment will be undertaken at the end of the program. It will take stock of all the learning dispensed and the learner’s level of autonomy. It will close with negotiations with the patient on an end-of-program contract and the definition of individual goals to be pursued at home.

- 1. Assessment criteria

### Main criterion

**Self-assessment questionnaire on quality of life specific to Parkinson’s disease**

Quality of life will be assessed using a specific scale (PDQ-39).

We will use the specific self-assessment measurement questionnaire, PDQ-39 (Parkinson's Disease Quality of Life) (De Boer et al., 1996). Its specific indicators are suited to detecting observable variations in the quality of life for a given disease, and in principle cannot be used to make comparisons between care programs that address different diseases (Carrere, 1997). The PDQ-39 is made up of 39 health-related questions that are to be answered retrospectively over a period of 1 month using 5 levels of frequency (always, often, sometimes, rarely, never). This specific quality of life measurement instrument assesses 8 dimensions of Parkinson’s patients’ health: mobility, everyday activities, emotional well-being, psychological stress, social support, cognitive disorders, communication and physical discomfort.

- 1. Secondary criteria

### General quality of life self-assessment questionnaire

We will use the general measurement self-assessment questionnaire, SF-36 (Medical Outcomes Study 36-item Short Form) (Ware et al., 1992). The SF-36 is made up of 36 items divided into 8 dimensions: physical functioning, limitations due to physical problems, emotions, social functioning, mental health, energy, pain and health perceptions. This self-assessment questionnaire has already been used for Parkinson’s disease (Riazi et al., 2003, Brefel-Courbon et al., 2003). It provides an assessment of quality of life among Parkinson’s patients and makes it possible to compare this condition with other populations (general population or patients suffering from a chronic disease).

### Motor scale: Unified Parkinson's Disease Rating Scale (Fahn et al., 1987)

The Parkinson’s patients will undergo an assessment of their motor condition using the Unified Parkinson's Disease Rating Scale (UPDRS) grid. The scale is made up of the following 6 sections: " mental, behavioral and thymic condition " (section I), "activities in everyday life during on and off periods" based on the patient interview (section II), "motor examination during on or off periods" according to the patient’s condition at the time of the visit (section III), "treatment complications" (section IV), "modified Hoehn and Yahr score" (section V), "modified Schwab and England scale concerning activities in everyday life" (section VI).

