Randomization will be performed after the inclusion visit. It will assign the patients to one of the two groups: group I: patients following therapeutic education sessions and group II: patient receiving simple conventional medical monitoring. It will be done after verification of the inclusion criteria. It should lead to the inclusion of the number of patients needed in the study groups. This randomization will be carried out by the Centre d’Investigation Clinique (Clinical Investigation Center) at Purpan Hospital.

- 1. Conduct of the study

Each patient in the study will participate for 12 months. The total duration of the inclusion period is planned to last 2 years.

- 1. Inclusion visit

This will be done at a normal neurology follow-up consultation and will include:

- obtaining free, informed consent from the patient;

- verification of the inclusion and exclusion criteria;

- the patient’s motor score (UPDRS in the On condition for Parkinson’s patients);

- general and neurological medical examinations;

- completing the self-assessment questionnaires;

- distribution of the notebook and explanations as to how to fill it in;

- gathering the patient’s characteristics, disease data (case history, related comorbidities) and medication consumption.

All travel between the home and the hospital for pre-inclusion, inclusion and follow-up visits will be covered by the CPAM as these visits will be part of the follow-up visits for their chronic neurological disease.

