### Follow-up and end-of-study visits

Patients will be assessed during a normal neurology follow-up consultation at 6 and 12 months after their inclusion.

During these 2 visits, the patient:

- will receive a neurological examination with a motor rating;
- fill in the self-assessment questionnaires;
- return the completed notebook and receive the notebook for the next visit (for the visit at 6 months).
  1. Data analysis

Data will be saved using the SAS software. The data input form will correspond exactly to the paper form used for gathering data.

The data will be made anonymous before its collation.

The statistical analysis will be descriptive as well as inferential:

- Qualitative variables will be described by presenting the frequency of each modality of these variables. Quantitative variables will be analyzed to establish the median, mean, standard deviation and extreme values.

- Quality of life will be analyzed classically using a linear model including a fixed treatment effect.

Comparisons of the medical costs, motor and psychological symptomatology (secondary quantitative assessment criteria) between two treatments will also be carried out in accordance with the process described above.

1. Expected consequences of the results of the project

If the impact of a TEP program is positive in terms of quality of life and if it does not produce additional costs, this type of care will be generalized for Parkinson’s disease and will give rise to contributions at national and international conferences.

1. Provisional schedule

Start of inclusions September 2008

End of inclusions September 2010

End of patient follow-up September 2011

Analysis of the results December 2011

1. Regulatory and ethical aspects

In accordance with law No. 2004-806 of 9 August 2004 relative to public health policy and its implementing orders, the project comes within the framework of an assessment of intermediate care and the study is subject to the opinion of a CPP (Comité de Protection des Personnes Sud-ouest et Outre-Mer – Institutional Review Board of the Southwest and Overseas Possessions). The research will not be implemented until a favorable opinion is received from the CPP.

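### The protocol gives no single rule for the motor state (On or Off) in which UPDRS section III is rated at inclusion, month 6 and month 12

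*Protocol*

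**What the plan says.** Three sections of the protocol bear on the motor rating.

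- **Motor scale (UPDRS), under the secondary criteria.** Section III is given as "motor examination during on or off periods", with the state decided "according to the patient’s condition at the time of the visit". No visit is excepted.
- **Inclusion visit.** The list of procedures includes "the patient’s motor score (UPDRS in the On condition for Parkinson’s patients".
- **Follow-up and end-of-study visits.** At 6 and 12 months the patient "will receive a neurological examination with a motor rating". No state is named.

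The experimental plan has neurologists do this at every visit: they "will carry out a clinical examination notably including a motor assessment". The secondary objectives are to "compare the motor condition, psychological condition, social adjustment and medical costs of two groups". The Data analysis section puts motor symptoms through the same process as quality of life, which is a linear model with a fixed treatment effect.

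**The concern.** For a patient who arrives Off at inclusion, the scale description and the inclusion list give different instructions for the same rating. At follow-up, the scale description is the only text that names a state, and it accepts either one. An On baseline may therefore be set against a follow-up score from a different state. Part of the apparent change in motor severity would then be a change in the state at examination.

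An analysis plan cannot repair this later. The state exists only at the moment of rating, and the protocol's lists of data to collect (Other clinical parameters, Inclusion visit, Follow-up and end-of-study visits) do not include it. At stake are the precision and comparability of one stated secondary comparison. The protocol also expects that a gain in quality of life may go with a motor gain, so the score has some bearing on how the main result is interpreted.

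**Working it through.** No figure in the plan depends on this point, so there is none to reproduce. The check is first of the text and then of possible size.

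**Text, by visit**

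| Visit | Scale description | Visit section | Result |
| --- | --- | --- | --- |
| Inclusion | On or Off, as the patient presents | On | The two conflict for a patient who is Off |
| Month 6 | On or Off, as the patient presents | no state | Either state is permitted |
| Month 12 | On or Off, as the patient presents | no state | Either state is permitted |

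If both visit sections are followed and the scale description fills the gap, the baseline is On and follow-up is On or Off.

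**Size, for illustration only**

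All inputs are assumptions, because the documents give neither an On/Off gap nor a share of patients rated Off:

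- gap D = 5 to 20 points on section III, the same for every patient;
- share of follow-up ratings done Off, p = 0.10 to 0.30, unrelated to the patient's On score;
- baseline ratings all On;
- where a relative figure is given, an On-state SD of 12 (variance 144).

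Shift in an arm's mean change from baseline = p × D:
- smallest: 0.10 × 5 = 0.5 points;
- largest: 0.30 × 20 = 6 points.

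Added variance of the follow-up score = D² × p × (1 − p):
- smallest: 25 × 0.10 × 0.90 = 2.25;
- largest: 400 × 0.30 × 0.70 = 84;
- at p = 0.20: D = 10 gives 100 × 0.16 = 16, and D = 20 gives 400 × 0.16 = 64. Against 144 these are +11% and +44%;
- over the whole grid: 2.25/144 = +2% to 84/144 = +58%.

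Shift in the between-group difference = (difference in p between arms) × D:
- equal shares Off in the two arms: 0, so only the added variance remains;
- shares that differ by 10 percentage points: 0.10 × 5 = 0.5 to 0.10 × 20 = 2 points, with no true motor effect.

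**The case against.** The strongest reply is that mixing of states is permitted but nowhere required. The scale description is an account of the instrument, and the on-or-off wording stands there inside the label of a section. The only visit-level instruction that names a state says On, and investigators could carry it forward to months 6 and 12. This stands in part: the text does not establish that states will be mixed. However, the phrase that ties the state to the patient's condition on the day lies outside the section label and reads as an instruction. The ambiguity is therefore real.

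A reader might go further and infer that the motor comparison is biased between groups, since the study is open and the programme might change the state in which patients attend. The documents do not support that as a finding. Both arms are rated under the same wording, so by default randomisation makes any mixing mainly noise. Adjusting doses to the motor state appears only as an example among the general purposes of therapeutic education, and the step-by-step description of the programme lists no module on it. Bias is possible but not shown.

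Two further objections stand. The study is declared pragmatic, so rating patients as they present is a defensible rule if it is applied at every visit. The size rests wholly on assumed inputs: eligibility requires treated disease at Hoehn and Yahr stage 4 or below, not motor fluctuations, so the share of patients with any relevant gap is unknown.

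**Conclusion.** The inconsistency holds on the text: On at inclusion, On or Off by presentation in the scale description, and no state named at follow-up. Nor is the state listed among the data to be collected; the case-report form is not at hand and could still contain it. The supported consequence is avoidable noise and weaker comparability with baseline in the secondary motor comparison.

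Under the assumptions shown, this is 0.5 to 6 points in an arm's mean change and 2.25 to 84 in variance. The between-group shift is 0.5 to 2 points only if the arms also differ by 10 percentage points in the share rated Off. These figures describe the assumptions and are not estimates for this trial. Confidence is high for the mismatch in wording and much lower for its effect.

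Two stronger conclusions should not be drawn: that scores will in fact mix states, and that the groups will differ because of it. The primary PDQ-39 comparison does not use this score and is unaffected. The change is worth making because it is cheap and because an unrecorded state cannot be recovered afterwards.

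**What to change.** Reconcile the UPDRS description, the inclusion-visit list and the follow-up section so that one rule on motor state applies to section III at inclusion, month 6 and month 12 in both groups. The choice of rule is the sponsor's; extending the rule already written for inclusion is one way. Record the state at each rating on the case-report form.

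For the analysis, keep all randomised patients in the motor comparison and adjust for the baseline score rated under the same rule. Do not restrict it to On-state scores. The state at a follow-up visit is observed after randomisation and may be influenced by the arm, so the restriction would select patients on it, and it could remove part of a real benefit if fewer patients in the programme attend Off. A comparison that takes account of the recorded state can serve as a sensitivity analysis.

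The cost is a change of wording in the protocol, one extra case-report-form item and, depending on the rule chosen, an occasional wait during a visit.
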